## Abstract

**Background:**

The recent guidelines from the European and American Hernia Societies recommend a continuous small-bite suturing technique with slowly absorbable sutures for fascial closure of midline abdominal wall incisions to reduce the incidence of wound complications, especially for incisional hernia. However, this is based on low-certainty evidence. We could not find any recommendations for skin closure. The wound closure technique is an important determinant of the risk of wound complications, and a comprehensive approach to prevent wound complications should be developed.

**Methods:**

We propose a single-institute, prospective, randomized, blinded-endpoint trial to assess the superiority of the combination of continuous suturing of the fascia without peritoneal closure and continuous suturing of the subcuticular tissue (study group) over that of interrupted suturing of the fascia together with the peritoneum and interrupted suturing of the subcuticular tissue (control group) for reducing the incidence of midline abdominal wall incision wound complications after elective gastroenterological surgery with a clean-contaminated wound. Permuted-block randomization with an allocation ratio of 1:1 and blocking will be used. We hypothesize that the study group will show a 50% reduction in the incidence of wound complications. The target number of cases is set at 284. The primary outcome is the incidence of wound complications, including incisional surgical site infection, hemorrhage, seroma, wound dehiscence within 30 days after surgery, and incisional hernia at approximately 1 year after surgery.

**Discussion:**

This trial will provide initial evidence on the ideal combination of fascial and skin closure for midline abdominal wall incision to reduce the incidence of overall postoperative wound complications after gastroenterological surgery with a clean-contaminated wound. This trial is expected to generate high-quality evidence that supports the current guidelines for the closure of abdominal wall incisions from the European and American Hernia Societies and to contribute to their next updates.

**Trial registration:**

UMIN-CTR UMIN000048442. Registered on 1 August 2022. https://center6.umin.ac.jp/cgi-open-bin/ctr_e/ctr_view.cgi?recptno=R000055205

## Introduction

### Background and rationale {6a, 6b}

Wound complications are among the most common morbidities for patients after gastroenterological surgery [1–4]. Short-term postoperative wound complications include incisional surgical site infection (SSI) [1, 2], hematoma, seroma, and wound dehiscence. Incisional hernia (IH) accounts for the majority of long-term postoperative wound complications [3, 4]. Both short-term and long-term wound complications are associated with a decreased quality of life, increased risks of morbidity and mortality, and dramatically increased medical costs [1–5]. Obesity, smoking, and old age are well-known risk factors for IH and highly overlap with the risk factors for SSI and wound dehiscence. Furthermore, SSI itself is an important risk factor for IH, and wound dehiscence may predict IH [6]. Thus, the pathogenesis and development of all wound complications may be correlated with each other, and a comprehensive approach to reduce the overall incidence of wound complications should be developed.

The wound closure technique that is used to close an abdominal wall incision is an important determinant of the risk of developing wound complications, especially in IH [3, 4]. The European Hernia Society proposed guidelines on the closure of abdominal wall incisions in 2015 [3], and it was recently updated by the European and American Society in 2022 [4]. For closure of the fascia, they recommend the combined use of a continuous small-bite suturing technique with slow absorbable sutures to reduce the risk of IH [3, 4].

Although the guidelines recommend the continuous suture technique, there has been no high-quality evidence suggesting the superiority of the continuous suture technique to the intermittent suture technique for the prevention of wound complications. Reliable recent meta-analyses that compared the interrupted and continuous suture techniques showed that there was no difference in the incidence of HH, wound dehiscence, or SSI [7, 8]. These meta-analyses included many smaller and older studies of low-certainty evidence; therefore, the evidence is of poor quality [7, 8]. Accordingly, for the establishment of high-quality evidence of wound closure techniques, further studies should be conducted to compare the impact of interrupted and continuous suture techniques in the prevention of wound complications.

For the closure of a midline abdominal wall incision (MAWI) in elective surgery, single-layer aponeurotic closure is recommended, but not mass closure in an all-in-one approach that includes the fascia, muscle, and peritoneum [3]. In a systematic review, there was no evidence of any short-term or long-term advantages of peritoneal closure during the closure of the laparotomy incision [9], and it was not recommended in the guidelines [3]. However, there was no evidence that mass versus layered closure increased the risk of IH, and no clinical studies directly comparing mass closure and a single-layer aponeurotic closure were found [3]. Thus, the recent recommendation appears to be based on low-certainty evidence, and further research is required to make strong recommendations [3, 4].

For skin closure, we could not find any recommendation for the prevention of wound complications. Subcuticular sutures for skin closure have been revealed to be associated with a lower incidence of wound complications and better cosmesis in clean wounds [10, 11]. In clean-contaminated wounds after gastroenterological surgery, subcuticular sutures were associated with a lower incidence of incisional SSI in comparison to staples in sub-analyses in some trials, but the effect of subcuticular sutures for preventing wound complications, including incisional SSI, has been controversial [12, 13]. A systematic review suggested that the use of continuous subcuticular sutures may reduce the risk of superficial wound dehiscence in comparison to interrupted sutures; however, there is uncertainty because of the quality of the evidence [14].

In gastroenterological surgery, MAWIs are widely used because they enable access to the whole abdominal cavity in open surgery. With the development of surgical technology since the 1990s, surgical procedures have progressed from open surgery to minimally invasive surgery, such as laparoscopic surgery and robotic surgery. With current surgical practices in developed countries, the proportion of minimally invasive surgery among gastroenterological surgeries is reported to be approximately 70% [15, 16]. Minimally invasive surgery has been revealed to reduce IH as an SSI [4]. However, the use of an MAWI as a specimen extraction site was found to be associated with a higher incidence of IH in comparison to nonmidline incision sites [4]. An MAWI is most frequently used as a site for specimen extraction in minimally invasive surgery because it achieves better cosmesis; thus, the development of an ideal method for MAWI closure after gastroenterological surgery is necessary for both open and minimally invasive surgery.

### Objective {7}

This single-center, prospective, randomized controlled trial (RCT) is being performed to evaluate the superiority of the combination of MAWI closure with continuous suturing of the fascia using a single-layer aponeurotic technique and continuous suturing of the subcuticular tissue for skin closure. The purpose of this trial is to establish the ideal combination of fascial closure and skin closure for reducing the overall incidence of MAWI wound complications after gastroenterological surgery.

### Study design {5a, 8}

This is a single-institute, prospective, randomized, blinded-endpoint trial being conducted to evaluate the superiority of the combination of continuous suturing of the fascia without peritoneal closure (single-layer aponeurotic closure) and continuous suturing of the subcuticular tissue over that of interrupted suturing of the fascia, together with the peritoneum and interrupted suturing of the subcuticular tissue, for reducing the incidence of MAWI wound complications after elective gastroenterological surgery with a clean-contaminated wound. This trial was designed and is being conducted by Saitama Medical Center, Jichi Medical University, and the present protocol follows the recommendations outlined in the Standard Protocol Items: Recommendations for Interventional Trials guidelines for RCTs (Supplementary Material 1) [17]. This trial was registered in the UMIN-CTR, and the WHO Trial Registration Data Set is included and can be found within the registry.

## Methods: participants, intervention, and outcomes

### Study setting {9}

Patients who receive elective gastroenterological surgery in the Department of Surgery, Saitama Medical Center, Jichi Medical University, and who are able to understand the extent and nature of this trial are eligible for inclusion in this study. This trial was approved by the Bioethics Committee for Clinical Research, Saitama Medical Center, Jichi Medical University (S22-001).

### Eligibility criteria {10}

The inclusion criteria are as follows:1.Scheduled to undergo elective surgery for the esophagus, stomach, duodenum, jejunum, ileum, colorectal, pancreas, liver, or biliary tract with a class II (clean-contaminated) surgical wound (Table 1)2. Age ≥ 18 years at the time of consent being obtained by nonblinded investigators.3. Scheduled to undergo computed tomography 1 year after surgery.4. Written informed consent provided.

**Table 1 Tab1:** Definition of the wound classes

Class I (clean)	An uninfected operation wound in which no inflammation is encountered and the respiratory, alimentary, and genitourinary tract is not entered
Class II (clean-contaminated)	An operative wound in which the respiratory, alimentary, and genitourinary tracts are entered under controlled conditions and without unusual contamination provided no evidence of infection or major break in technique is encountered
Class III (contaminated)	A wound in which gross contamination/spillage and a break in sterile technique occurs, and an incision in which acute, nonpurulent inflammation is encountered
Class IV (dirty-contaminated)	A wound that is already considered infected, such as old traumatic wounds with retained devitalized tissue or perforated viscera

The exclusion criteria are as follows:1. Emergency surgery.2. Age < 18 years.3. A history of midline abdominal wall incision.4. A history of abdominal incisional hernia or fascial tear.5. Identification of bacterial infection in the surgical field or the use of antibiotic therapy prior to the operation.6. Presence of a contaminated abdominal cavity due to stoma, intestinal fistula, or drainage tube.7. Open wound management for prior operation.8. Synchronous operation for more than two targeted organs.9. Current immunotherapy (≥ 40 mg of a corticosteroid per day or azathioprine).10. Chemotherapy within 14 days prior to surgery.11. A history of abdominal radiotherapy.12. Pregnancy.13. Registered for another clinical trial.14. Conditions that make the patient unsuitable for inclusion according to the judgment of nonblinded investigators.

### Who will take informed consent? {26a}

Nonblinded investigators who received ethics education and were approved by the Bioethics Committee for Clinical Research, Saitama Medical Center, Jichi Medical University, will obtain informed consent for surgery and inclusion in the clinical trial after admission, 1–2 days before surgery. Adequate time will be given to participants to consider their decision regarding trial participation. Subsequently, participants can sign the informed consent form, and they can withdraw at any time during the trial.

### Additional consent provisions for collection and use of participant data and biological specimens {26b}

Patient characteristics, such as sex, age, body mass index, serum albumin level, comorbidities, American Society of Anesthesiologists-physical status classification and preoperative treatment, will be collected. In addition, surgical data, such as the surgical procedure, operative time, estimated blood loss, wound classification, and length of postoperative hospital stay, will be collected. Additional biological specimens will not be collected for this trial. The investigators do not expect to conduct ancillary studies requiring the use of participant data that is collected in this study.

### Interventions

#### Intervention description {11a}

Study group:MAWI closure with continuous suture of the fascia without peritoneum (single layer aponeurotic technique) and continuous suture of the subcuticular tissue for skin closure.

Control group:MAWI closure with interrupted suture of the fascia with the peritoneum and interrupted suture of the subcuticular tissue for skin closure.

In the study group, the fascia is sutured continuously with 1-STRATAFIX SYMMETRIC PDS plus (Ethicon, Johnson & Johnson, Somerville, New Jersey, USA) without the peritoneum. Continuous subcuticular suture is then used for skin closure using 4–0 STRATAFIX Spiral PDS plus (Ethicon, Johnson & Johnson, Somerville, New Jersey, USA). In the control group, the peritoneum and fascia are sutured together using interrupted sutures with 1-PDS plus (Ethicon, Johnson & Johnson, Somerville, New Jersey, USA). Interrupted subcuticular sutures are then used for skin closure using 4–0 PDS plus (Ethicon, Johnson & Johnson, Somerville, NJ, USA). In both groups, narrow and closed fascia sutures, where each suture will be placed approximately 5–9 mm from the edge of the fascia and approximately 5 mm from the adjacent fascia suture, are recommended. Suturing of the fascia and subcuticular tissue is applied from both ends of the incision toward the center or applied from one end to the other end according to the operator’s direction during the operation.

#### Criteria for discontinuing or modifying allocated interventions {11b}

There are no predominant criteria for discontinuing or modifying the intervention assigned to participants. All individuals are participating on a voluntary basis, and they have the option to withdraw from the study at any time for any reason without facing any negative consequences.

#### Strategies to improve adherence to interventions {11c}

All participants who meet the criteria will receive a participant information sheet from the investigators before giving their written informed consent. By enrolling participants who were scheduled to undergo computed tomography 1 year after surgery, we ensured that adherence to the study protocol would improve. Furthermore, participants will be informed of the significance of completing follow-up assessments.

#### Relevant concomitant care permitted or prohibited during the trial {11d}

The following measures are used to prevent SSI in our protocol:1. Surgical skin antisepsis with aqueous 10% povidone–iodine solution is performed before skin incision.2. Standard antibiotic prophylaxis is administered 30 min before making the skin incision with additional doses every 3 h for patients with a normal renal function.3. The use of a wound protector is recommended.4. Surgical gloves are changed before skin suture.5. Intraoperatively and postoperatively, a normal body temperature is maintained using warming devices and appropriate oxygenation.6. Intraoperative wound irrigation was performed for 1 min with 40 mL of aqueous 10% povidone–iodine (POVIDONE–IODINE solution 10% “MEIJI”; Meiji Seika Pharma Co, Ltd, Tokyo, Japan).7. Perioperative glycemic control is implemented with a blood glucose target level of < 200 mg/dL.

All suture materials were antimicrobial-coated slowly absorbable monofilaments. Before the initiation of and during the trial, investigator meetings were held several times, and the treatment protocol was fully disseminated to all investigators. Investigators who were not familiar with continuous suture techniques were trained in the required skills using pig abdominal wall models and performed operations under the direction of surgeons who were familiar with the technique before participating in the trial. The principal investigator is responsible for all trial-related issues and questions.

All participants will receive standard postoperative care management during hospitalization and throughout the duration of the study.

#### Provisions for posttrial care {30}

There are no provisions for participants who participate in the trial. Posttrial care follows the standards of care after surgery.

### Outcomes {12, 18a}

#### Primary outcome

The primary outcome is the incidence of wound complications, including incisional SSI, hemorrhage, seroma, and wound dehiscence within 30 days after surgery and IH at approximately 1 year after surgery. Nonblinded investigators will check the surgical wound and describe the medical records during hospitalization. If wound complications are suspected based on the clinical findings, nonblinded investigators will record the treatment details in the medical record. After discharge, participants will be referred to the outpatient department approximately 30 days after surgery. Participants will be recommended to contact us and visit the outpatient department soon if they experience any symptoms suggesting wound complications. Nonblinded investigators will examine the patients in the same way as during hospitalization. One year after surgery, participants will be referred to the outpatient department, and the incidence of incisional hernia will be assessed with a physical examination by nonblinded investigators and computed tomography (CT) of the abdomen. The blinded assessors will determine the presence or absence of wound complications according to the clinical records.

Incisional SSI is defined according to the standard criteria devised by the CDC [18]. Incisional SSI includes superficial and deep incisional SSI that develops during the first 30 days after surgery. Superficial incisional SSI involves the skin or subcutaneous tissue at the incision site, and deep incisional SSI affects more internal structures of the abdominal layer (such as the fascia or muscle). Wound hemorrhage is defined as superficial postoperative wound bleeding or subcutaneous hematoma. Seroma is defined as a collection of serous fluid in the subcutaneous space, detected either clinically or by imaging. Wound dehiscence includes superficial dehiscence and total dehiscence. Superficial dehiscence is defined as skin-only dehiscence. Total dehiscence is defined as a dehiscence of the entire abdominal wall. IH is defined as any abdominal wall gap with or without a bulge in the area of a postoperative scar that is perceptible or palpable by clinical examination or imaging according to the European Hernia Society guidelines [19].

#### Secondary outcomes

The secondary outcomes are the duration of abdominal wall closure and wound pain on postoperative day (POD) 7. Nonblinded operating surgeons and nurses will measure and record the duration of abdominal wall closure, wound length after the completion of wound closure, and the number of operating surgeons involved in wound closure. The duration of wound closure is defined as the time from the application of the first suture needle to the wound until the suture is finished and the thread is cut. A questionnaire using a 10-point numerical rating scale is used for the estimation of wound pain [20]. It is documented by the participant on POD7 and is collected by blinded investigators.

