## Assignment of interventions: allocation

### Sequence generation {16a}

Participants will be registered, randomized, and allocated by nonblinded investigators. Participants’ data will be password-protected and will only be accessible by investigators. All access to the secure separate database will be monitored and logged. Permuted-block randomization with an allocation ratio of 1:1 and blocking will be used. The randomization will be stratified by sex, surgical organ (upper gastrointestine, small bowel, colorectum, hepatobiliary–pancreas, and others), and surgical approach (laparotomy or laparoscopy).

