## Statistical methods

### Statistical methods for primary and secondary outcomes {20a}

All analyses will be performed after the termination of the main part of the trial, that is, after the last 1-year follow-up visit has taken place. We will perform the primary analyses using the full analysis set, from which patients who do not undergo surgery or who withdraw their consent before the assessment of the primary endpoint are excluded (modified intention-to-treat set). In addition, we will repeat the analyses in the per-protocol set, further excluding patients with major protocol deviations. Student’s *t* test or the Mann–Whitney *U* test will be used to compare continuous variables with a normal or nonnormal distribution. The *χ*^2^ test or Fisher’s exact test will be used to compare categorical variables between the study group and the control group. *P* values of < 0.05 were considered to indicate statistical significance. All statistical analyses will be conducted using EZR [23].

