### Method for additional analyses (e.g., subgroup analyses) {20b}

Subgroup analyses will be performed for the surgical approach (laparotomy or laparoscopy). *P* values of < 0.05 will be considered statistically significant.

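### Closure time and day-7 pain are to be compared by unadjusted tests that ignore the randomization strata; the tests stay valid, but for closure time they are likely to be conservative and to lose power

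*Protocol article*

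**What the plan says.** - Protocol article, Secondary outcomes: "The secondary outcomes are the duration of abdominal wall closure and wound pain on postoperative day (POD) 7". Closure time is total elapsed time, "the time from the application of the first suture needle to the wound until the suture is finished and the thread is cut". On who records it, and what is recorded alongside: "Nonblinded operating surgeons and nurses will measure and record the duration of abdominal wall closure, wound length after the completion of wound closure", and also the number of surgeons closing. No use is stated for wound length or for the number of surgeons.
- Statistical methods {20a}: Student's t or the Mann-Whitney U "test will be used to compare continuous variables with a normal or nonnormal distribution". No stratum, covariate or stratified test is named.
- Sequence generation {16a}: permuted blocks, 1:1, stratified by sex, five organ groups "and surgical approach (laparotomy or laparoscopy").
- Additional analyses {20b}: "Subgroup analyses will be performed for the surgical approach (laparotomy or laparoscopy"), with no outcome named.
- Background {6a, 6b}: "the proportion of minimally invasive surgery among gastroenterological surgeries is reported to be approximately 70"%, a general literature share, with the midline wound then often serving as the extraction site.

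**The concern.** Both arms are to space fascial sutures about 5 mm apart (Intervention description {11a}), so suturing work should grow with incision length. A pooled comparison of open and extraction wounds then carries much variation that is due to approach and not to technique.

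Stratified allocation removes most of that variation from the difference between arms. An unadjusted test still counts it in the standard error. The result is a confidence interval that is too wide and a test that rejects less often than its nominal 5%. A real saving in closure time could be missed although the design already holds the information needed to show it.

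Choosing between two tests by the look of the distribution also leaves the effect measure for these outcomes open.

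**Working it through.** **The plan's own figure.** Rates of 29.2% and 14.6%, two-sided 0.05, 80% power, pooled variance under the null, mean rate 0.219:

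n per arm = [1.96·√(2·0.219·0.781) + 0.8416·√(0.292·0.708 + 0.146·0.854)]² / 0.146² = (1.146 + 0.485)² / 0.0213 ≈ 124.8, so 125 per arm and 250 in total. Then 250/0.98/0.90 = 283.4, so 284. The plan's figures reproduce, and this point does not affect them. No effect size, SD or power is stated for closure time.

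**Model for closure time (all inputs assumed).** 30% open; log time = 0.8 × log length + error; SD of log length within approach 0.24; residual log-SD s; N = 250. Three variance parts:

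- between approaches: B = 0.3·0.7·[0.8·ln(open length / laparoscopic length)]²
- length within approach: W = (0.8·0.24)² = 0.0369
- residual: R = s²

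Reported unadjusted SE = √[(4/250)(B+W+R)]. With approach balanced by design, the estimate actually varies by about √[(4/250)(W+R)], which is also the SE after adjusting for approach. The SE therefore falls by 1 − √(1 − share), where share = B/(B+W+R).

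| Median lengths, s | B | R | Share | SE unadjusted | SE adjusted | Fall |
|---|---|---|---|---|---|---|
| 20 and 6 cm, 0.3 | 0.1948 | 0.0900 | 0.61 | 0.072 | 0.045 | 37% |
| 15 and 6 cm, 0.5 | 0.1128 | 0.2500 | 0.28 | 0.080 | 0.068 | 15% |
| 10 and 6 cm, 0.5 | 0.0351 | 0.2500 | 0.11 | 0.072 | 0.068 | 6% |

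First row as an example: √(0.016 × 0.3217) = 0.0717 and √(0.016 × 0.1269) = 0.0451. The true null rejection rate of the unadjusted test is 2[1 − Φ(1.96 × 0.0717/0.0451)] ≈ 0.2%. For a 10% shorter closure (−ln 0.9 = 0.105), power is Φ[(0.105 − 1.96 × 0.0717)/0.0451] ≈ 22% unadjusted and Φ[0.105/0.0451 − 1.96] ≈ 65% adjusted.

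**Check by simulation.** 3,000 trials per cell of the table below, allocated over the plan's 2 × 5 × 2 = 20 strata. Block size 4 and the organ mix are further assumptions.

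| Scenario | Null rejection: Mann-Whitney / adjusted | Power at 10% shorter: t on minutes / Mann-Whitney / adjusted for approach |
|---|---|---|
| 20 and 6 cm, 0.3 | 0.6% / 4.3% | 15% / 23% / 64% |
| 15 and 6 cm, 0.5 | 1.9% / 4.2% | 18% / 21% / 33% |
| 10 and 6 cm, 0.5 | 3.5% / 4.6% | 25% / 29% / 34% |

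The closed form and the simulation agree within about two percentage points on adjusted power.

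The range is not a bound. Under another assumed model (time = 3 + length, 30% or 50% open, residual CV 20% to 60%), approach explained 0.12 to 0.72 of the variance. By the same formula that is a fall of 6% (1 − √0.88) to 47% (1 − √0.28).

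No calculation is offered for day-7 pain: the documents give nothing on its spread or its relation to the strata.

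**The case against.** **The unadjusted test is valid, and an unseen analysis plan may adjust.** The first part stands. When allocation was simulated without stratification, rejection under no effect was about 5% to 7% for t, Mann-Whitney and covariance analysis alike; with stratification the unadjusted tests fall below 5%. On the second part, the article does not leave the matter silent. It states a rule, and that rule omits the strata used at randomization.

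**The subgroup analysis by approach already separates long from short wounds.** Only in part. It names no outcome, splits the sample and gives no pooled adjusted estimate.

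**Stronger readings that a reader might infer:**

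- *Wound length will dominate the variance of closure time.* The documents give no distribution of either. Under the assumed mixes, length explained anything from 0.21 to 0.85 of it.
- *A chance imbalance in incision length would read as a technique effect.* Approach, the likely main driver of length, is balanced by design. What remains within approach is ordinary sampling error, which the 5% level already covers.
- *Adjusting is worth more than three times the sample.* In the first scenario, (0.0717/0.0379)² ≈ 3.6 compares an overstated unadjusted SE with one adjusted for length and approach. Against the estimate's real variability the ratio is (0.0451/0.0379)² ≈ 1.4, and most of the loss is recovered by adjusting for approach alone.
- *Since wound length is recorded, it belongs in the main model.* Randomization precedes surgery (Participant timeline {13}), and nonblinded staff measure length after closure. Technique could affect it.

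**Conclusion.** The point holds as one of precision, not of bias or false positives. The stated analysis ignores the stratification, so for closure time it overstates the standard error and yields a conservative test. In the scenarios shown, with 30% open cases and 250 patients, adjusting for approach cuts the reported SE by about 6% to 37%. It lifts power for a 10% shorter closure from about 21-29% (Mann-Whitney) to about 33-64%.

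The direction follows from the design, provided approach affects closure time. The size depends on incision lengths, case mix and residual spread that the documents do not give. For day-7 pain the same argument applies in principle, and the gain may be small. The primary outcome and the sample size are untouched, so the change is desirable but not essential.

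**What to change.** Prespecify, before the blinded biostatistician analyses the data:

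1. **Closure time:** linear regression of log closure time on arm and the stratification factors (at least approach, with sparse organ strata combined), reporting the ratio of times with a 95% CI.
2. **Day-7 pain:** the comparison between arms adjusted for the same factors.
3. **Test choice:** these models replace the choice between t and Mann-Whitney by distribution.
4. **Sensitivity analysis only:** add log wound length to the closure-time model.
5. **No adjustment** for the number of closing surgeons, which technique may influence.

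The cost is a few sentences of plan wording and a little extra analysis. The stratification factors are known for every randomized patient, so no new data are needed. The downside is reliance on a log-linear model for closure time.
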